**Figure 4 F4:**
[figure not shown]
(A) Distributions of trait variance explained by a single marker from Doehring *et al*
44 for traits included in our study and those not included. (B) Allele frequency distributions of loci associated with experimental pain in previously published cohorts, for Europeans and Colombians.

Power of a GWAS depends on the allele frequency of the SNPs through their effect on the test statistic. While the majority of GWAS studies are conducted in European-origin individuals, including the experimental pain study used to determine sample size here,^44^ our population of interest is an admixed Latin American population. Therefore, we wanted to assess the distribution of allele frequencies in Europeans versus Colombians for SNPs studied for or associated with experimental pain in various studies.^44 45^ Minor allele frequencies were obtained for all such reported SNPs from the 1000 Genomes project database^17^ for Western Europeans (from Britain (GBR), Utah residents from Northern and Western Europe (CEU), Spain (IBS), and Tuscany in Italy (TSI)) and Colombians (from Medellin in Colombia, (CLM), where this study will be performed). Allele frequency distributions for both Europeans and Colombians are shown in figure 4B. The two distributions are quite similar, with the Colombian distribution slightly more spread out. This is somewhat expected as the Colombians have on average 60% European (Spanish) ancestry.^26^ Having a well spread out distribution of allele frequencies is important in a GWAS as low-frequency alleles have lower power for a given sample and effect size.^46^ Here, the comparison to European allele frequency distribution suggests that the current Colombian cohort will have nearly equivalent power to any European-based cohort. In contrast to European-only cohorts though, our cohort will have the advantage that alleles present in other continental populations such as sub-Saharan Africans or Native Americans that are not present in Europeans would also be detectable in a GWAS, and could be followed up in replication cohorts of specific ethnicities.

The CANDELA project includes genotpyes of ~2000 patients from Medellin. We anticipate to contact and phenotype 50%–75% of these participants as well as contacting an additional 500 participants to bring the initial sample to 1500–2000.

#### Data analysis plan

The cleaned genetic data will first be merged with reference samples worldwide, such as the 1000 Genomes Project,^17^ Simons Genome Diversity Project,^47^ Estonian Biocentre Human Genome Diversity Panel,^48^ and additional European and Native American samples that are particularly relevant for Latin American populations.^49^ The merged dataset will be checked for genetic outliers, through genetic PCs and continental ancestry proportions (using supervised Admixture^50^), and for unexpected genetic similarities. These steps can often detect any sample misplacement or contamination, which might be reflected in sex mismatch, unexpected genetic similarities or inflated heterozygosity rates.^40 51^ Genetic ancestry estimates will be compared with self-reported ancestry information (see online supplementary appendix 1), particularly for genetic outliers or samples showing unexpected results. Participants self-reporting for ethnicities rare in Colombians, such as East Asian or South Asian, would also be excluded as outliers. The authors have extensive experience in conducting association analysis in admixed populations, including several GWAS publications on a wide range of phenotypes which contain detailed protocols on how to conduct such analyses.^27 39 52 53^ Further details of the currently used quality control protocol for CANDELA samples^53^ are provided in online supplementary appendix 2.

The genetic data allow estimation of the narrow-sense heritability of any quantitative trait, which is the fraction of trait variance that is explained by the genetic data. Estimates of heritability, obtained using the software GCTA,^54^ will provide an idea of which traits have more of a biological basis versus which are more environmentally determined, and thus which traits would be more amenable to genetic analysis for discovery of associated genetic variants. Note however that relatively precise estimate (low SDs) of heritability by this method requires several thousand samples,^52^ so the currently proposed sample size might be underpowered to estimate heritability accurately.

To facilitate better identification of associated loci, the genotype data will be imputed to approximately 10 million loci using the 1000 Genomes phase 3 imputation reference panel^52^ by first haplotype phasing using SHAPEIT2^55^ and then imputation using Impute2.^56^ Quality control of the imputed genotypes will be performed using recommended thresholds on imputation quality score, concordance metrics and proportion of high-probability calls. Details of the currently used imputation protocol for CANDELA samples^52^ are provided in online supplementary appendix 2.

GWAS studies will be conducted in Plink2^57^ to perform single-locus association studies for each trait individually, across the whole genome in an additive multivariate linear regression model.^42^ Covariates will be used in the regression to adjust for any other sources of trait variability, such as basic variables like age, sex, and BMI, and genetic PCs will be used to control for population substructure.^52 58^

The number of genetic PCs to be included in the regression depends on the sample composition, such as variation in ancestry and presence/absence of genetic outliers. It would be determined by inspecting the proportion of variance explained by each PC (displayed on a scree plot) and by checking PC scatter plots.

In addition to being used as exclusion criteria, anxiety and depression scores could be used as covariates in GWAS. The exact set of covariates to be used will be determined based on initial diagnostic analyses such as correlation analysis.

These single-locus association results, obtained as p values, will be visualised via the Manhattan plot. Commonly used p value thresholds for selecting associated loci are 5×10^−8^ for genome-wide significance and 10^−5^ for suggestive significance.^42^

An extension of this additive multivariate linear regression model, still within the single-trait single-locus setting, called the mixed linear model analysis which better controls for any cryptic relatedness or population substructure, will also be performed in GCTA.^54^

There are several extensions of the single-trait single-locus association studies that increase power for detecting associated loci: combining several related traits that may share a biological basis, using multivariate Wald tests as implemented in MultiPhen^59^; or gene-based tests that combine signals across all loci in a gene to increase signal strength and reduce the burden of multiple testing, such as set-based models implemented in Plink2^57^ or fastBAT implemented in GCTA.^60^ The admixed nature of the sample might be used in detecting associations by the method of admixture mapping,^61^ though the potential of success of this method in detecting associated variants depends on the extent of stratification of the variant’s allele frequency across continents. These analyses might help detect additional loci that are underpowered in classical GWAS due to smaller effect sizes.

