### Participants

Healthy participants aged 18–40 will be recruited in Medellin, Colombia via public noticeboards at local Universities, distribution of flyers and through the local print media. In addition, we are inviting previous participants from the Consortium for the Analysis of the Diversity and Evolution of Latin America (CANDELA)^26^ GWAS to participate in this project.

Recruiting healthy young participants has advantages in GWAS studies. They are less likely to have undetected illnesses or other problems that may influence their biological pathway of pain sensitivity. Young people will also have less overall accumulated exposure or risks from environmental (external) factors which may affect their pain sensitivity. Such factors increase the overall variability of participants’ pain perception response and reduce the power of detecting genetic causes. Since most traits are affected by a combination of genetic and environmental factors, many studies including CANDELA tend to use young participants for genetic variant discovery.^27^

Participants will be excluded if they have chronic pain or any chronic medical condition (eg, diabetes, neurodegenerative, musculoskeletal or psychiatric conditions). Participants currently taking analgesics, anti-inflammatories, opioids, antihistamines, antidepressants or antiepileptic drugs will be excluded. Women who are pregnant or in their menstrual phase (self-report) will be excluded from the study. Participants will be advised to not smoke or consume coffee within 1 hour of testing, and to avoid psychoactive substances or alcohol within 8 hours prior to testing. Further exclusion criteria include current or past self-inflicted injuries, as well as dermatomal, traumatic or infectious conditions affecting the arm, and a history of severe allergic reactions to any kind of medication, materials, food or insect bites. Participants with moderate to severe anxiety (≥25 on the Hamilton Anxiety Rating Scale^28^) or severe depression (>15 on the 16-item Quick Inventory of Depressive Symptomatology Self-Reported (QIDS-SR16)^29^ will be excluded from the study. Recruitment started in January 2013 and is predicted to take approximately 5–7 years.

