### Procedure

Participants will attend a single appointment at the quantitative sensory testing (QST) laboratory at the Universidad de Antioquia, Medellín. Following informed consent, age and self-reported gender will be recorded and participants will answer questions regarding their self-reported ancestry (see online supplementary appendix 1). Height and weight will be measured and body mass index (BMI) calculated. Since psychological factors such as anxiety can influence pain perception during experimental pain testing,^30^ participants will complete the Spanish version of the Hamilton Anxiety Rating Scale and the QIDS-SR16. The QIDS-SR16 has acceptable internal consistency and moderate to strong concurrent validity compared with other depression scores^31^ and its Spanish version shows adequate test–retest reliability and high internal consistency.^32^ The Hamilton Anxiety Rating Scale has shown to have high inter-rater and test–retest reliability^33^ and good construct validity.^34^

10.1136/bmjopen-2018-025530.supp1Supplementary data

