### Genotyping

Each participant will donate blood or saliva (Oragene OG-500, Genotek, Canada) for DNA extraction. DNA samples will be genotyped on the Illumina HumanOmniExpress chip containing ~700 000 markers. In volunteers who already participated in the CANDELA GWAS,^39^ genotype data from blood samples genotyped on the same chip are already available and will be reused.

Whole-genome genotype data from the Illumina array will undergo quality control^40^ to exclude any markers or samples that fail stringent thresholds. Quality metrics provided by the genotype calling algorithm in the Illumina GenomeStudio software,^41^ such as the GenTrain score, cluster separation score, and excess heterozygosity rates will be used to filter poorly genotyped SNPs. Subsequent SNP-level and sample-level quality control thresholds such as missingness will be applied. Sex mismatch between records and genetic data of X and Y chromosomes will be checked. Only samples and SNPs that pass all criteria will be retained for analysis. Details of the currently used quality control protocol for CANDELA genotyped samples are provided in online supplementary appendix 2.

10.1136/bmjopen-2018-025530.supp2Supplementary data

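### The self-reported ancestry exclusion appears only in the analysis plan, although the answer is known before any painful test is given

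*Protocol article*

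**What the plan says.** All references are to the protocol article.

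- **Data analysis plan.** After describing the genetic checks on the merged data ("The merged dataset will be checked for genetic outliers, through genetic PCs and continental ancestry proportions"), the section adds: "Participants self-reporting for ethnicities rare in Colombians, such as East Asian or South Asian, would also be excluded as outliers". The two groups named are examples; no closed list is given.
- **Procedure.** There is one visit: "Participants will attend a single appointment at the quantitative sensory testing (QST) laboratory". The ancestry questions come near its start: "Following informed consent, age and self-reported gender will be recorded and participants will answer questions regarding their self-reported ancestry". The Hamilton Anxiety Rating Scale and the QIDS-SR16 are described in the same paragraph. The sections on sensory testing and mustard oil follow.
- **Participants.** The entry exclusions begin with "Participants will be excluded if they have chronic pain or any chronic medical condition" and go on to medication, pregnancy and menstruation, self-inflicted injury, conditions of the arm, allergy, anxiety and depression. Two of them use questionnaire scores from the visit, for example "Participants with moderate to severe anxiety (≥25 on the Hamilton Anxiety Rating Scale". None concerns ancestry or ethnicity.
- **Evaluation of sensory function in the naïve state** and **Mustard oil evoked nociceptive sensitisation.** Each participant has the baseline battery, 30% mustard oil on the forearm for 10 minutes with pain scored every 30 seconds, mapping of flare and hypersensitivity, and repeat mechanical and heat pain thresholds.

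**The concern.** An exclusion that depends only on what a person says before testing can be applied before testing. Here it is stated solely among the analysis steps. Someone following the text would ask the question, record a disqualifying answer, carry out the whole noxious protocol, and have the data removed later. The article names no other use for those data.

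Two things are at stake, both modest:

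- **Burden.** Healthy volunteers would bear deliberately evoked pain without contributing to the result.
- **Capacity.** One trained examiner does all the phenotyping, recruitment is expected to last about 5 to 7 years, and the article itself describes the sample as limited. Each slot given to a person who cannot be analysed is lost to the 1500 to 2000.

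There is also a smaller point of specification. Because the rule is given by example, which other self-reported groups it covers would be settled after the pain data exist. An entry criterion would force the list to be fixed first.

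**Working it through.** **1. Order of events in the text.**

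| Step | Section | Ancestry rule applied? |
|---|---|---|
| Entry exclusions | Participants | No ancestry criterion |
| Consent, then ancestry questions and anxiety and depression scales | Procedure | Answer recorded, not acted on |
| Baseline sensory tests | Evaluation of sensory function in the naïve state | No |
| Mustard oil, mapping, repeat thresholds | Mustard oil evoked nociceptive sensitisation | No |
| Genetic checks and exclusion on self-report | Data analysis plan | Yes, the only place |

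The anxiety and depression scales are the useful comparison. They are completed at the same point of the visit as the ancestry questions, and their scores are entry exclusions. Screening on answers given at the visit is therefore already part of the design.

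**2. The plan's own sample size.** Inputs from Sample size calculation: about 2000 CANDELA participants, 50% to 75% of them phenotyped, plus 500 others.

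- Lower end: 0.50 × 2000 + 500 = 1500
- Upper end: 0.75 × 2000 + 500 = 2000

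The stated 1500 to 2000 is reproduced.

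**3. How many people could be affected.** The documents give no share; the only description is that these ethnicities are rare. The shares below are assumptions. Number tested and then excluded = share × n.

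| Assumed share | n = 1500 | n = 2000 |
|---|---|---|
| 0.1% | 1.5 | 2 |
| 1% | 15 | 20 |
| 3% | 45 | 60 |

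The range is about 2 to 60 people.

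**4. Whether power is at risk.** For a 1-df test at 5×10⁻⁸, take the non-centrality parameter as n·q²/(1 − q²), where q² is the share of trait variance explained by the marker. The q² that gives 80% power is 2.57% at n = 1500 and 1.94% at n = 2000. Hold q² fixed and reduce n by the excluded share:

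| Share lost | Power (same at both sample sizes) |
|---|---|
| 0 | 80.0% |
| 0.1% | 79.9% |
| 1% | 79.1% |
| 2% | 78.2% |
| 5% (beyond the range assumed above) | 75.2% |

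An assumed loss of 1% costs 80.0 − 79.1 = 0.9 percentage points. A 3% loss lies between the 2% and 5% rows. For a group described as rare, the statistical effect is small. The case for change rests on burden and use of slots.

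**The case against.** **The timing is inferred from where the sentence stands.** The exclusion sentence carries no time point. Figure 1, which sets out the procedure from recruitment to analysis, and appendix 1, which holds the ancestry questions, are not shown. An earlier screen there cannot be ruled out. This stands as a limit on how firmly the point can be put. It does not remove it: the article gives a detailed list of entry exclusions and a separate ancestry exclusion, and the second is absent from the first.

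**The effect is small and validity is untouched.** This also stands. The same people are left out of the analysis whenever the rule is applied, the share is unknown, and no stated figure changes. It keeps the point minor.

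**A stronger reading does not hold.** A reader might go on from the Genotyping section, which says that for former CANDELA participants "genotype data from blood samples genotyped on the same chip are already available and will be reused", to argue that genetic outliers and relatives among them could be screened out before invitation. These volunteers make up 1000/1500 = 67% to 1500/2000 = 75% of the planned sample. The documents do not support that step, for four reasons:

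- The merged-data checks are presented largely as a way of detecting sample mix-ups and contamination. No removal rule is stated for unexpected similarity, and cryptic relatedness is left to a mixed linear model.
- Similarity between a returning volunteer and a new recruit cannot be known until the recruit is genotyped.
- Using stored genotypes to choose whom to invite would come before this study's consent, which is taken at the appointment. The article does not say that the CANDELA consent covers it, so it cannot be called a cheap change.
- The 67% to 75% is the share with genotypes on file. It is not the share who would be excluded.

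**Conclusion.** The point holds for the self-report rule only. As the article is written, volunteers whose recorded answer already excludes them would undergo the pain battery and mustard oil for data that the plan then discards. Severity is minor: a cheap improvement that spares some volunteers needless exposure and saves a few testing slots.

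The size, about 2 to 60 of 1500 to 2000, rests wholly on an assumed share of 0.1% to 3%; the word rare points to the lower part of that range. The conclusion also assumes that no earlier ancestry screen is set out in the figure or appendices that are not shown, and that the excluded data serve no other purpose, since none is named.

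It should not be read as a finding that most of the sample could be genetically pre-screened, that genetic checks are misplaced at the analysis stage, or that the study's power is compromised.

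**What to change.** 1. Add the self-reported ancestry exclusion to the entry criteria under Participants, with the excluded categories named in full instead of by example.
2. State under Procedure that it is applied after the ancestry questions and before the first sensory test, in the same way as the anxiety and depression scores.
3. Leave the genetic-outlier and similarity checks in the Data analysis plan. Keep the comparison of self-reported with genetic ancestry there too, since it can only be made once genotypes are in hand.
4. If an earlier screen is already in use, a sentence saying so is enough.

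The cost is an eligibility sentence, a closed list of categories and a small protocol or ethics amendment. The ancestry questions are already asked at the right moment, so no new procedure is needed. Recruitment began in January 2013, so the change would benefit only people not yet tested.

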## Abstract

**Introduction:**

Pain constitutes a major component of the global burden of diseases. Recent studies suggest a strong genetic contribution to pain susceptibility and severity. Whereas most of the available evidence relies on candidate gene association or linkage studies, research on the genetic basis of pain sensitivity using genome-wide association studies (GWAS) is still in its infancy. This protocol describes a proposed GWAS on genetic contributions to baseline pain sensitivity and nociceptive sensitisation in a sample of unrelated healthy individuals of mixed Latin American ancestry.

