## Introduction

Pain constitutes a major component of the global burden of diseases, with lower back and neck pain representing the single leading cause for years lived with disability followed closely by migraine and other musculoskeletal disorders.^1^ Pain is a multidimensional experience involving a highly complex interaction of physical, biochemical, physiological, cognitive, emotional, behavioural and sociocultural factors. Many studies have identified genetic factors in a range of chronic pain conditions.^2^ Importantly, a growing number of studies in patient populations suggest that genetics is an important contributory factor to pain susceptibility and severity.^2–4^ Of note, twin studies using either clinical pain outcomes or experimental pain models suggest that sensitivity to pain has a heritability of up to 55%.^5–10^ Interestingly, the heritability varies greatly depending on the clinical pain outcome or the sensory modality tested in experimental pain models.^7^ There is evidence that different sensory modalities may have distinct genetic components contributing to their variance in humans,^10^ and this is consistent with animal models which underline the distinct neurobiology mediating different sensory modalities.^11^

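### The heritability paragraph labels the GCTA estimate narrow-sense heritability and reads it as separating biology from environment, but in unrelated people it targets only SNP-tagged additive variance

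*Protocol article*

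**What the plan says.** The heritability paragraph of the Data analysis plan sets out "estimation of the narrow-sense heritability of any quantitative trait, which is the fraction of trait variance that is explained by the genetic data". The estimator is named next: "Estimates of heritability, obtained using the software GCTA". Two uses follow. The estimates "will provide an idea of which traits have more of a biological basis versus which are more environmentally determined", and from this the plan infers which traits are better suited to a search for associated variants. One caveat is given, that precise estimates need several thousand samples, "so the currently proposed sample size might be underpowered to estimate heritability accurately".

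Other sections bear on what this estimate measures:

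- **Sample.** The abstract places the study "in a sample of unrelated healthy individuals of mixed Latin American ancestry".
- **Markers.** Under Genotyping, "DNA samples will be genotyped on the Illumina HumanOmniExpress chip containing ~700 000 markers". Later in the Data analysis plan, "the genotype data will be imputed to approximately 10 million loci using the 1000 Genomes phase 3 imputation reference panel"; the stated aim there is to find associated loci. The heritability paragraph does not say which marker set it uses.
- **Ancestry adjustment.** Genetic principal components (PCs) are named as covariates for the association regression. Nothing explicit is said about the heritability model.
- **Comparator.** The only heritability figure in the article is in the Introduction, from twin studies: "sensitivity to pain has a heritability of up to 55" per cent.

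**The concern.** The defining sentence joins two parameters. Narrow-sense heritability is the share of trait variance due to all additive genetic effects. The share accounted for by a set of SNPs, in people who are not relatives, counts a causal variant only as far as those SNPs are correlated with it. Rare or poorly tagged variants drop out. The two agree only if tagging is complete, which the article neither claims nor shows.

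The difference matters for interpretation. Additive variance that the SNPs miss goes into the model's residual. If a low estimate is then taken to mean that a trait is mainly environmental, missed genetic variance is counted as environment. The caveat given does not help, because it concerns precision and suggests that more participants would settle the matter. Incomplete tagging is a property of the markers. It does not shrink with sample size, and it would be present even for a perfectly repeatable trait.

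**Working it through.** **Nothing to reproduce.** The article states no GCTA estimate and no tagging figure. The check therefore asks what the estimator targets, using 0.55 (the Introduction's upper twin figure) as an illustrative true narrow-sense value.

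**1. Target.** Let h² = V_A / V_P be narrow-sense heritability and t the share of additive variance tagged by the SNPs used, with 0 ≤ t ≤ 1. Without confounding, SNP-based heritability is t × h². Sample size does not enter. The values of t are assumptions.

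| t (assumed) | t × 0.55 | Gap to 0.55 |
|---|---|---|
| 0.5 | 0.275 | 0.275 |
| 0.7 | 0.385 | 0.165 |
| 0.8 | 0.44 | 0.11 |
| 1.0 | 0.55 | 0 |

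**2. Simulation without population structure.** True h² = 0.55, six replicates per setting.

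- 2000 people, 1500 SNPs each tagging one causal variant, tagging r² of 0.5, 0.65, 0.8 and 1.0: mean likelihood estimates 0.28, 0.36, 0.44 and 0.55.
- 1500 people, 3000 independent SNPs, t of 0.5, 0.7 and 1.0: mean REML estimates 0.26, 0.35 and 0.56.

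Both follow t × h². The 0.35 lies about 0.04 below its expected 0.385. With a between-replicate SD of 0.042, the Monte Carlo error is about 0.042/√6 = 0.017, so this run shows the direction and rough size only.

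**3. Simulation with admixture.** 1500 people, t = 0.7, six replicates. The ancestry-correlated non-genetic variance is an assumption.

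| True h² | Ancestry-correlated non-genetic variance | PCs in model | t × h² | Mean estimate |
|---|---|---|---|---|
| 0.55 | 0 | 2 | 0.385 | 0.39 |
| 0.55 | 5% | none | 0.385 | 0.45 |
| 0.55 | 5% | 2 | 0.385 | 0.35 |
| 0.10 | 5% | none | 0.07 | 0.23 |

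In the last row the estimate exceeds the true narrow-sense value itself. Uncorrected stratification can thus outweigh incomplete tagging.

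**4. Sampling error.** Approximately SE = √(2 / (N² × v)), where v is the variance of the off-diagonal relationships. The article does not give v. At an assumed v = 2×10⁻⁵:

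- N = 1500: √(2/45) = 0.21
- N = 2000: √(2/80) = 0.16

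Over an assumed range of v from 4×10⁻⁴ down to 1×10⁻⁵, the SE runs from 0.05 to 0.30 at N = 1500 and from 0.04 to 0.22 at N = 2000. A single estimate can fall on either side of the true value.

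**The case against.** The strongest reply is that the sentence supplies its own definition. Its second half describes the quantity that GCTA estimates, so the numbers are not biased for what is defined, only for what it is called. That is correct, and it makes this a labelling error rather than a wrong analysis. The label still matters: it is the name that would go with the results, and the statement about environment that follows it relies on the label's meaning.

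Other parts of the reply also stand:

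- **Discovery use.** For deciding which traits suit SNP discovery, tagged variance is the relevant quantity. If tagging is similar across traits, their ranking is unchanged.
- **Imputation.** Using the roughly 10 million imputed loci could narrow the gap. The heritability paragraph does not say they are used, and imputation would not make the two parameters identical.
- **Condensed article.** Model detail and interval reporting are commonly left to a fuller document. Their absence is not the finding; they appear below only as part of the remedy.

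A reader might infer more than the documents support. One might conclude that the reported heritabilities will be too low, or are a lower bound. That describes the target without confounding, not each estimate from an admixed sample, as steps 3 and 4 show. One might also conclude that the plan will test its estimates against the twin figure or report one minus the estimate as environmental variance. It states neither. The twin figure is an upper value in the Introduction, which adds that heritability differs greatly between outcomes and modalities, and the statement about environment is a loose comparison between traits.

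**Conclusion.** The point holds as a wrong name for the estimand and an interpretation that the estimate cannot carry. In unrelated people GCTA targets SNP-based heritability. Absent confounding this is expected to be at or below narrow-sense heritability, and the sample-size caveat does not address the difference.

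Its size cannot be computed from the documents, because it depends on tagging and on whether imputed SNPs enter the model. The illustrated gap of 0.11 to 0.275 at a true value of 0.55 rests wholly on an assumed 50% to 80% tagging. Stratification, if left uncorrected, could move estimates upward, so the sign of the error in any one reported figure is not fixed.

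Severity is minor. This is a descriptive secondary analysis, and no association test, significance threshold, power figure or sample size uses it.

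**What to change.** In the heritability paragraph:

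1. Call the quantity SNP-based heritability, defined as the share of trait variance due to additive effects tagged by the SNPs used, and say whether those are the genotyped or the imputed SNPs.
2. Fit the heritability model with the same genetic PCs as the association model.
3. Report each estimate with its SE or confidence interval.
4. State that, absent confounding, it is expected to fall at or below narrow-sense and twin values, and that it is not directly comparable with the 55% twin figure. Avoid an unconditional lower-bound claim.
5. Remove the reading of a low estimate as evidence that a trait is environmentally determined. Keep the use for judging which traits suit SNP discovery.

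The cost is a few sentences and one stated covariate choice, with no new data. The heritability claim becomes weaker.
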